**Methods and analysis:**

At least 234 adult patients with newly diagnosed epilepsy will be recruited from 14 centres in Australia. Patients will be randomised 1:1 to the ML group or usual care group. The ML group will receive the ASM recommended by the model unless it is considered contraindicated by the neurologist. The usual care group will receive the ASM selected by the neurologist alone. Both the patient and neurologists conducting the follow-up will be blinded to the group assignment. Both groups will be followed up for 52 weeks to assess treatment outcomes. Additional information on adverse events, quality of life, mood and use of healthcare services and productivity will be collected using validated questionnaires. Acceptability of the model will also be assessed.

The primary outcome will be the proportion of participants who achieve seizure-freedom (defined as no seizures during the 12-month follow-up period) while taking the initially prescribed ASM. Secondary outcomes include time to treatment failure, time to first seizure after randomisation, changes in mood assessment score and quality of life score, direct healthcare costs, and loss of productivity during the treatment period.

This trial will provide class I evidence for the effectiveness of a ML model as a decision support tool for neurologists to select the first ASM for adults with newly diagnosed epilepsy.

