## Methods and analysis

### Study design and setting

This is a multicentre, randomised, controlled, patient and assessor blinded trial conducted in Australia. It is considered ‘first-in-class’ as the first RCT of an ML model in epilepsy management. Adults of working age with newly diagnosed epilepsy will be referred to the study by their treating clinicians. Participants will be recruited from 14 epilepsy centres across 5 Australian states from 14 February 2024 to 13 February 2026.

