### Randomisation and ASM prescription

The participant will be randomised 1:1 into either the experimental (ML group) or the control group (usual care group) using individual randomisation centralised and in blocks that are stratified by both seizure type (focal vs generalised onset) and study site. In the experimental group, EpiMD will be run using the information provided and respond with the ASM recommendation. The investigator will prescribe the recommended ASM unless it is considered to be contraindicated due to safety reasons. In this case, the investigator will prescribe a different ASM and provide their reasoning for doing so. In the control group, the recommendation by the ML model will not be revealed, and the investigator will prescribe an ASM based only on their clinical judgement.

Any out-of-pocket costs associated with new generation ASMs used as monotherapy that are not covered by the Pharmaceutical Benefits Scheme will be reimbursed to the participants. ASM prescription will be open label for both groups. Guidance regarding the rate of titration, initial maintenance dose and any subsequent increments or decrements will be made available to the prescribing clinician. If the patient is taking an ASM prior to randomisation, the drug will be ceased over 2–4 weeks under the supervision of the treating neurologist.

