### Statistical analysis

Analysis of efficacy will be done for the intention-to-treat (ITT) set (all randomised patients who have taken at least one dose of the prescribed ASM) and the per-protocol set (patients in the ML group for whom neurologists did not prescribe the recommended drug will be excluded). The Cochran-Mantel-Haenszel test stratified by centres (to account for variation between centres) will compare the differences in 12-month seizure-free rate; retention rate (affected by both efficacy and tolerability) of the initial treatment at 1 year; and proportion of patients who achieve clinically meaningful improvement in quality of life. Cox regression will be used to assess differences in time to treatment failure and time to first seizure after treatment initiation between the two groups. Prescription patterns of the two groups will be compared. In the ML group, we will also compare the outcomes between patients who are prescribed the ML recommended ASMs and those who are prescribed non-ML recommended ASMs by their neurologists. This will include analysis of the reason provided by the neurologists in cases where ML recommendation was rejected. Also, the outcomes of different ASM groups such as sodium channel blockers versus non-sodium channel blockers will be compared.

Validation of EpiMD in the control group will be done by comparing the predicted response to the neurologist-selected ASM treatment outcome. A probability threshold of 0.55 will be applied in classifying treatment success or failure to calculate the model’s sensitivity, specificity and area under the curve.

To assess cost-effectiveness in the economic evaluation, cost differences and effect differences for 10 000 bootstrap draws will be analysed from the trial dataset over a 1-year time horizon. This will be represented using a cost-effective plane and a cost-effectiveness acceptability curve.^26^ This analysis will be performed both from the public healthcare and societal perspective. Consideration was given to the inclusion of an elderly cohort, particularly due to the prevalence of epilepsy in this age group. However, to match the current retirement age, we intend to maintain the upper age limit of 67. Based on the analytic results, future study directions such as extended follow-up duration will be considered, and given the distinct health and social needs of the older adult population,^27^ we propose the future development of a model specific to this cohort.

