### Sample size

Based on previous RCTs in newly diagnosed epilepsy^29^,^32^ and observation in the Glasgow and Perth cohorts,^4 33^ the 12-month seizure-free rate on the first ASM in the usual care group is assumed to be 35% and to follow a distribution of Binomial (1000, 0.35) in participating sites. In keeping with ILAE recommendations for detecting clinically significant benefit,^34^ we hypothesise that the ITT 12-month seizure rate will be 20% higher (ie, 55%) when EpiMD is used. Allowing for non-compliance with the recommended drug by the investigators in 10% of patients in the ML group, with a one-sided significance level of 0.025 and 80% power, accounting for 10% dropout, a total of 234 participants (117 patients per group) will be recruited, determined from the 95th percentile of 1000 simulations. This will provide 90% power to detect a 23% higher ITT 1-year seizure rate in the ML group. This sample size will provide 80% power for the same minimal detectable effect size in retention rates and proportion of patients who report clinically meaningful improvement in QOLIE-31 total score. Additionally, this will provide for a minimum detectable HR of 0.58 in exit due to lack of efficacy, adverse events or any reason, and time to first seizure, assuming overall at least 50% event rates.

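### Randomisation is stratified by seizure type and site, but the Cochran-Mantel-Haenszel test is stratified by centre only, and no reason is given for leaving seizure type out

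*Protocol article*

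**What the plan says.** The section on randomisation and ASM prescription allocates participants "in blocks that are stratified by both seizure type (focal vs generalised onset) and study site". The abstract gives the ratio: "Patients will be randomised 1:1 to the ML group or usual care group". The study setting gives the number of sites: "Participants will be recruited from 14 epilepsy centres across 5 Australian states".

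The Statistical analysis section names the test and its stratifier: "The Cochran-Mantel-Haenszel test stratified by centres (to account for variation between centres"). That one test covers the 12-month seizure-free rate, retention on the initial treatment at one year, and the proportion with a clinically meaningful gain in quality of life. The section explains why centre is included. It does not explain why seizure type is not.

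The strengths and limitations list mentions a planned subgroup analysis by focal and generalised epilepsy. No section gives seizure-free rates by type or says how strongly type predicts outcome.

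**The concern.** Blocks formed within seizure type and site hold the two arms close to balance on seizure type. Any difference in seizure freedom between focal and generalised onset is then largely removed from the treatment comparison by design. A test that ignores seizure type still counts that difference as random error. If type is prognostic, the standard error is somewhat too large, the test rejects slightly less often than its nominal level under the null, and some power is lost. The error runs in the safe direction, so what is at stake is efficiency and agreement between design and analysis.

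This is not a detail left to a later plan. The protocol fixes the stratifier, so an analysis plan that follows it inherits the omission.

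**Working it through.** **Step 1. The plan's own sample size.** Inputs from the Sample size section: "the 12-month seizure-free rate on the first ASM in the usual care group is assumed to be 35" per cent; "we hypothesise that the ITT 12-month seizure rate will be 20% higher (ie, 55%) when EpiMD is used"; "with a one-sided significance level of 0.025 and 80% power"; 10% non-compliance; 10% dropout.

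- Per arm: n = [0.35×0.65 + 0.55×0.45] × (1.960 + 0.842)² / 0.20² = 93.2, rounded up to 94.
- 94 / (0.9 × 0.9) = 116.05, rounded up to 117 per arm, or 234 in total. The stated figure is reproduced.
- Power at 117 × 0.81 = 94.8 per arm is 79.5% for 20 points and 89.4% for 23 points, matching the stated 80% and 90%.

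No gain from adjusting for seizure type is built into 234.

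**Step 2. How conservative the test can become.** Let f be the share with generalised onset, and p0 and p1 the focal and generalised success rates, averaging 35%. With perfect balance on type, the true variance relative to the one the test uses is

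r = [(1−f)·p0(1−p0) + f·p1(1−p1)] / (0.35×0.65),

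and the actual one-sided error is 1 − Φ(1.960/√r). With f = 30% (assumed):

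| Odds ratio for type | p0 | p1 | r | Error |
|---|---|---|---|---|
| 2 | 0.301 | 0.463 | 0.976 | 0.0236 |
| 3 | 0.273 | 0.530 | 0.939 | 0.0216 |
| 5 | 0.238 | 0.610 | 0.872 | 0.0179 |

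With f = 50% the errors are almost the same (0.0235, 0.0214, 0.0179). Incomplete blocks make real balance less than perfect, so the true effect should generally be smaller than this.

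**Step 3. Centre-only test against an additive model.** Simulated trials with 234 randomised, 14 unequal sites, 30% generalised, blocks of 4, 10% dropout and a 35% control rate. The spread between sites is √(0.35×0.65/1000) = 1.5 percentage points, read from the Binomial (1000, 0.35) assumption in the Sample size section. The additive model is a linear probability model with arm, site and type. There were 10,000 null and 6,000 alternative trials per row (Monte Carlo standard error about 0.0016 for error and 0.5 points for power). Each cell shows centre-only / additive.

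| Odds ratio | One-sided error | Power, +20 points | Power, +18 points |
|---|---|---|---|
| 1 | 0.025 / 0.026 | 83.5 / 83.2% | 73.7 / 73.8% |
| 2 | 0.024 / 0.025 | 83.2 / 83.9% | 75.1 / 76.1% |
| 3 | 0.023 / 0.026 | 84.1 / 86.0% | 74.8 / 76.8% |
| 5 | 0.018 / 0.022 | 84.3 / 87.8% | 75.1 / 79.3% |

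The gain is nil at odds ratio 1, 0.7 to 1.0 points at 2, 1.9 to 2.0 at 3 and 3.5 to 4.2 at 5. The 18-point column is a sensitivity case (20 × 0.9). Power at 20 points exceeds 80% because these trials remove dropout only: the formula in Step 1 gives 83.6% at 117 × 0.9 = 105.3 per arm.

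**Step 4. Centre-only test against the fully crossed test.** Crossing gives 14 × 2 = 28 cells, with 234/28 = 8.4 randomised and about 7.5 evaluable patients each. With 30% generalised and a between-site standard deviation of 0.3 on the logit scale:

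| Odds ratio | Power at +20 points, centre only → crossed |
|---|---|
| 1 | 83.5 → 82.6% |
| 2 | 84.1 → 83.6% |
| 3 | 84.0 → 85.1% |
| 5 | 84.5 → 86.7% |

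About 5 to 10% of patients fall in cells that carry no information, against about 1% with centre alone. Crossing therefore costs about 1 point when type is not prognostic.

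**Step 5. Stability.** At 25% focal and 58% generalised success, the odds ratio is (0.58/0.42)/(0.25/0.75) = 4.1. Separate sets of simulated trials there put the centre-only error at 0.019, 0.0195 and 0.0233. The direction is firm; the exact size depends on assumptions, such as site sizes, that the protocol does not fix.

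**The case against.** The case for leaving the test alone has real weight, and most of it stands.

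- **Strength of the factor.** A reader might infer that seizure type is strongly prognostic because it was chosen for stratification and for a subgroup analysis. Neither choice is evidence of that, and the protocol gives no rates by type. At an odds ratio of 2 or less the centre-only error is close to nominal and the power at issue is about 1 point or less.
- **Power.** A reader might infer that power is already tight and that the omission pushes it below target. The documents do not support this. The figure of 234 reproduces without any covariate gain, and the protocol states 20 points as the intention-to-treat effect. At that effect the centre-only test has about 83 to 84% power when only dropout is removed. Whether 10% non-compliance should dilute the effect to 18 points is a separate question.
- **Sparse cells.** With 14 centres, crossing with seizure type is thin, so stratifying by centre alone is a defensible choice. This counts against the crossed test but not against an additive model, which shows no detectable loss at an odds ratio of 1.
- **Cox models.** A reader might infer that these are unadjusted, because they are described only as comparing "time to treatment failure and time to first seizure after treatment initiation between the two groups". That is silence about covariates, which an analysis plan may fill, and it is no part of this point.

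What the objection does not answer is that the protocol names a single stratifier for the primary test, uses two in the design, and gives no reason for the difference.

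**Conclusion.** The point holds as a modest mismatch between design and analysis. The centre-only test introduces no bias and no inflation of type I error, and the sample size stands. If seizure type is prognostic, the test is mildly conservative and gives up about 1 point of power or less at an odds ratio of 2, about 2 points at 3, and up to about 4 points at 5, measured against an additive model. If it is not prognostic, nothing is lost.

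These sizes rest on assumptions outside the documents: 30% generalised onset, blocks of 4, unequal site sizes and the seizure-type odds ratio itself. They were worked out for the primary outcome. The same mismatch applies to retention and QOLIE-31 response, but no size was computed for those.

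**What to change.** Include both randomisation factors in the analyses of 12-month seizure freedom, retention and QOLIE-31 response, in a form that handles sparse cells. A suitable choice is an additive binary model with arm, seizure type and site that reports a standardised risk difference, with a rule fixed in advance for very small sites. The gains in Step 3 are for a linear probability version; a logistic version should behave similarly but was not simulated. Do not use the fully crossed 28-cell test. If the sponsor prefers the centre-only test, the protocol should say why seizure type is omitted.

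The change is wording only, since both variables are already collected for randomisation. It should be settled before unblinding. The small downside is a model-based primary analysis in place of a simple Cochran-Mantel-Haenszel test; that test could be kept as a sensitivity analysis.

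### The unexplained 0.55 cut for validating EpiMD lies 20 points above the assumed 35% control success rate, and the measures named with it cannot reveal overprediction; adding calibration is a cheap improvement

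*Protocol article*

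**What the plan says.** The Statistical analysis section sets out a validation of the model in the usual care arm: "Validation of EpiMD in the control group will be done by comparing the predicted response to the neurologist-selected ASM treatment outcome". It then fixes the method: "A probability threshold of 0.55 will be applied in classifying treatment success or failure", and this is done "to calculate the model’s sensitivity, specificity and area under the curve". No source or reason for 0.55 is given.

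The Sample size section says that "the 12-month seizure-free rate on the first ASM in the usual care group is assumed to be 35" per cent, and hypothesises a rate "20% higher (ie, 55%) when EpiMD is used". The cut is thus 20 points above the assumed success rate of the group in which it is applied, and has the same value as the hypothesised rate of the other arm.

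The Introduction describes the model as predicting and ranking the likelihood of success on each of seven drugs. The ML model section says that the score for each drug is kept for later analysis. The article gives no AUC, score spread or calibration result for EpiMD.

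**The concern.** Calibrated probabilities have a mean equal to the true success rate. If that rate is 35% in controls, a calibrated EpiMD averages 0.35 on the drugs the neurologists chose, and 0.55 lies in the upper tail. Sensitivity and specificity at that point then depend heavily on the distance between cut and base rate, as well as on how well the model separates successes from failures.

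Two misreadings could follow. A sound model could show low sensitivity and be taken as poor. A model whose probabilities run too high could show a more balanced pair and be taken as better. AUC does not settle the matter, because it depends only on ranking. The validation is meant to show how far the predictions can be trusted in new patients, and the three named measures leave the level of the predictions untested.

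**Working it through.** **Inputs from the article.** Cut 0.55 (Statistical analysis). Control success rate 0.35, ML-arm rate 0.55, 117 per group, 10% dropout, 10% non-compliance with the recommendation (Sample size). Seven candidate drugs (Intervention).

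**Inputs assumed.** Calibration in controls, a beta shape for the predictions, and an AUC between 0.60 and 0.80. The article gives none of these.

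**The plan's own figure.** The article states no sensitivity or specificity, so there is none to reproduce. The 35% is the rate the design works with: 35% versus 55%, one-sided 0.025 and 80% power give 106 per arm with continuity correction, and 106 × 1.10 = 116.6, that is 117.

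**Calibrated model.** Let the prediction p follow Beta(mk, (1−m)k) with m = 0.35, and let success occur with probability p. Then:

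- share called success = P(p > 0.55)
- sensitivity = P(Beta(mk+1, (1−m)k) > 0.55)
- specificity = P(Beta(mk, (1−m)k+1) ≤ 0.55)

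For each AUC, k is solved so that p has that AUC against the outcome.

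| Assumed AUC | k | SD of p | Called success | Sensitivity at 0.55 | Specificity at 0.55 |
|---|---|---|---|---|---|
| 0.60 | 34.1 | 0.08 | 0.9% | 1.5% | 99% |
| 0.65 | 14.7 | 0.12 | 5.8% | 10% | 96% |
| 0.70 | 7.9 | 0.16 | 12% | 22% | 93% |
| 0.75 | 4.7 | 0.20 | 18% | 34% | 91% |
| 0.80 | 2.9 | 0.24 | 22% | 45% | 90% |

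A logit-normal shape gives similar sensitivities: 13% at AUC 0.66, 24% at 0.70 and 33% at 0.74.

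**A spread tied to the plan's own hypothesis.** Suppose the gain from 35% to 55% comes from taking the best of seven independent calibrated probabilities, with the control choice no better than random. Allowing for 10% non-compliance, the target for the best drug is 0.55 to 0.35 + 0.20/0.90 = 0.572. This needs an SD of about 0.14 to 0.155, which implies an AUC of about 0.68 to 0.69 and a sensitivity of about 16% to 21%.

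**The same ranking with inflated scores.** Take the AUC 0.65 model and multiply every predicted odds by (0.55/0.45)/(0.35/0.65) = 1.222/0.538 = 2.27. The ranking and AUC stay the same. The mean prediction rises to 0.54 against a true 0.35. A score of 0.55 now corresponds to a true probability of 0.35.

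| AUC 0.65 | Mean prediction | Sensitivity at 0.55 | Specificity at 0.55 | Sensitivity + specificity − 1 |
|---|---|---|---|---|
| Calibrated | 0.35 | 10% | 96% | 0.07 |
| Odds inflated 2.27-fold | 0.54 | 62% | 60% | 0.21 |

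The 19-point overprediction is invisible in the AUC and gives the higher sum of sensitivity and specificity. The calibrated model read at a cut of 0.35 also gives 62% and 60%, so the whole difference comes from where the cut falls.

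**A milder case.** If the scores were trained to a 50% base rate, 0.55 corresponds to true odds of 1.222 × 0.538 = 0.658, a probability of 0.40. Sensitivity is then about 47% to 62% for AUC 0.65 to 0.75.

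**Precision.** 117 × 0.35 = 41 successes in controls, or 117 × 0.90 × 0.35 = 37 after 10% dropout.

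**The case against.** A reader might infer that the plan guarantees a sensitivity near 10% and that almost every control will be called a failure. The article does not support that. The figure needs an AUC close to 0.65 (0.64 to 0.66 gives 8% to 12%) together with calibration, and neither is stated. A reader might also take 0.55 as an error because it exceeds the base rate. It is not one in itself: a high cut trades sensitivity for specificity, and if 0.55 comes from model development, testing it unchanged in new patients is proper external validation.

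The plan reports sensitivity, specificity and AUC together, so a careful reader would see a low sensitivity beside a high specificity. AUC from the continuous score does not depend on the cut. EpiMD recommends the top-ranked drug, so any miscalibration that preserves the order leaves every recommendation unchanged. Calibration measures may stand in an analysis plan that is not shown, so their absence from an article is no fault. All of this stands, and it limits the point to a supportive analysis.

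It does not remove the point. The article itself fixes the cut and names the measures, and those measures give 10% and 96% or 62% and 60% for models that rank patients identically. A reader holding only these results could not tell which case applied. That the scores might not be calibrated to 35% is a further reason to report calibration.

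**Conclusion.** The point holds as a cheap improvement. The 20-point gap and the lack of a stated reason for 0.55 follow directly from the article. The size of the effect is conditional: with calibrated predictions averaging 0.35, sensitivity at 0.55 is about 1% to 34% for AUC 0.60 to 0.75 and 45% at 0.80, with specificity from about 99% down to 90%. With scores that run high it is far larger at the same AUC. The firm conclusion is that the named measures cannot separate weak discrimination from a cut that does not match the base rate, cannot detect overprediction, and can favour it. The primary comparison and the sample size do not use the cut and are unaffected.

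**What to change.** Keep 0.55 as the pre-specified cut and state where it came from. State that AUC is computed from the continuous score. Beside these, report for the control-arm predictions the mean predicted against the observed success rate, the calibration intercept and slope with confidence intervals, a smoothed calibration plot, and the Brier score. Report sensitivity and specificity also at a second cut of 0.35, the control rate assumed for the sample size, fixed before unblinding.

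The cost is wording in the analysis plan and a few lines of analysis on scores the trial already keeps. There are two drawbacks. Two cuts are reported instead of one, and 0.35 will itself miss the base rate if the true control rate differs. With about 37 to 41 successes among at most 117 controls, the calibration slope and plot will be imprecise, so they should be read with their intervals and not as a pass-or-fail test.
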